#### Qualitative modules BEA and IDEE

Participants of the module BERNA who have consented to be contacted regarding a qualitative module are called or contacted via e-mail depending on the details they provide. Depending on their availability via phone, call attempts can be repeated up to two times within a 2-week period or at a more convenient time as expressed by the participant. Participants are then informed about either IDEE or BEA, receive a written information about the study via e-mail, and are asked about their preferences regarding the date of the interview or World Café.

For IDEE, districts assigned to the three strata with at least three BERNA participants interested each are chosen first for interview planning. If less than three interviews can be conducted in those districts, participants from other districts assigned to the same stratum are contacted. Participants are offered the options of a telephone interview or an interview at a local venue close to their neighborhood for a one-on-one conversation. They receive a mobile text or a phone call as a reminder prior to the agreed-upon date and give written consent sent by post or at the physical meeting, respectively.

For BEA, the rural and the nonrural district with most BERNA participants interested in participating in a qualitative study are chosen as the location for the World Café event. The date and time for which most participants in a district are available is chosen at a venue close by. All participants receive a reminder via phone call or mobile text 1 week as well as 2 days prior to the event. They are informed about the conditions of the study again at the event and are asked to give their written consent before the start of the event.

After finishing the interview or the World Café, participants receive a remuneration of 30 Euro in cash or as a voucher for a supermarket of their choice.

#### Quantitative module KENNER

Similar to BERNA, participants in the KENNER survey are also enrolled in three steps. At first, one district for each of the three strata is randomly drawn. Then, food banks in these districts are purposively sampled and food bank managers receive written information about the study and are asked to allow the recruitment of adults with children in their facility. Food banks that agree to participate are visited by trained study staff. All adults visiting the facility during the visit of the study staff are verbally informed about the aim, the study procedures, and data protection measures. Individuals willing to participate are screened for inclusion into the study using a checklist.

Participants receive a remuneration of 5 Euro for completing the questionnaire.

### Data collection and data collection instruments

#### Quantitative module BERNA

The data collection method of the module BERNA consists of self-administered questionnaires for parents and for youths aged between 12 and 17 years. Data of younger children are assessed by the parents. Participants needing assistance in answering the questionnaires and participants with low literacy or other obstacles in reading/writing are interviewed.

Parents are asked to collect cash receipts of their food shopping over a period of 2 weeks.

Table 2 demonstrates the variables assessed by the questionnaires. Sociodemographics of parents and sociodemographics of children and youths as well as diverse health and nutritional aspects are assessed by a slightly adapted version of questionnaires from the KiGGS (Hölling et al., 2012) and the DEGS (Scheidt-Nave et al., 2012). Adaption was necessary to cover, for instance, all family forms (e.g. initial answer options of the question “With whom does your child mainly live?” only include heterosexual partners) and to cover school meals and meals in daycare facilities (by adding “at the day care center (e.g. KITA) or at school” into the initial question “Does your child have the option of getting a warm lunch at school?”).

**Table 2. table2-02601060241242159:** Variables assessed by standardized questionnaires per household in the quantitative BERNA module.

	**Unit**				
**Domains**	**Adult respondent**	**Both parents**	**Child aged 1–11 years^1^**	**Youth aged 12–17 year**	**Household**
**Sociodemographics**	Age, sex	Country of birth, year of immigration, nationality, employment status, parental occupation, educational level	Age, sex, country of birth, year of immigration, visited childcare facility/type of school attended	Age, sex, country of birth, year of immigration, visited childcare facility/type of school attended	Number of adults and children living in the household, income
**Health and health behavior**	Subjective health status, chronic diseases, physical activity	Smoking status, weight, and height	Subjective health status (parents’ perspective), weight and height, physical activity	Smoking status, subjective health status, weight and height, physical activity	
**Nutritional aspects**	Aspects of nutrition knowledge, subjective cooking skills and source of learning cooking skills, planning food shopping, planning meal preparation, frequency of cooking, social dimensions of food insecurity		Usage of childcare/school meals including frequency and reasons for nonusage, meal participation in youth clubs	Usage of school meals including frequency and reasons for nonusage, meal participation in youth clubs	Food insecurity (past 30 days), family meals including type and frequency, usage of “Tafel” food bank including frequency and duration of use, usage of soup kitchen
**Diet**	Food Frequency Questionnaire		Food Frequency Questionnaire	Food Frequency Questionnaire	

^1^
Data of children aged between 1 and 11 years are assessed by the parents.

Subjective cooking skills and source of learned cooking skills are assessed by slightly adapted questions of the computer-assisted personal interview applied in the NVS II (Max Rubner-Institut, 2005a). For instance, for convenience reasons, answer options “my mother” and “my father” were combined into “my mother / my father.” Aspects of nutrition knowledge are assessed by the questionnaires from the NVS II (Max Rubner-Institut, 2005b, 2008).

Household food insecurity over the past 30 days is measured using the Food Insecurity Experience Scale (FIES) provided by the Food and Agriculture Organization (FAO) of the United Nations (Cafiero et al., 2016). The FIES consists of eight questions and covers the access dimension of food insecurity including psychological (e.g. worrying about not having enough food; “During the past 30 days was there a time when you or others in your household worried about not having enough food to eat because of a lack of money?”), qualitative (e.g. eating only a few kinds of food), and quantitative aspects of food insecurity (e.g. skipping a meal). Answer options include “yes,” “no,” “don’t know,” and “refused.” As recommended by the FAO, statistical validation will be conducted to test whether the data are consistent with the theoretical construct the FIES is based on (Cafiero et al., 2016). Based on the number of affirmative responses, each respondent will then be assigned to categories of food insecurity. To assess the social domain of food insecurity, four questions of the Four Domain Food Insecurity Scale are used (e.g. feeling embarrassed) (Johnson et al., 2020). Answer options include “agree a lot,” “agree a little,” “disagree a little,” and “disagree a lot.” Respondents with zero affirmative answers (“agree a lot” or “agree a little”) will be categorized as social food secure, respondents with one to three affirmative answers will be categorized as mildly social food insecure and respondents who confirm all four questions will be categorized as severely social food insecure.

Planning food shopping and food preparation are assessed by three items each (e.g. making a shopping list to guide food purchases; planning cooking in advance) of the Food Related Lifestyle Inventory (Scholderer et al., 2004).

For the assessment of adults’ diet the semiquantitative food frequency questionnaire (FFQ) of the DEGS study (Scheidt-Nave et al., 2012) is used and for children and youths, the FFQ of the KiGGS is applied (Hölling et al., 2012). The development of the KiGGS FFQ is based on the DEGS FFQ, details are described elsewhere (Mensink and Burger, 2004). In short, the KiGGS FFQ “What does your child eat” covers 48 food items including beverages, the youth version “What do you eat?” and the DEGS FFQ covers 54 food items including alcoholic beverages. All versions ask the average food frequency over the past 4 weeks and the average consumed portion size per food item. Categories for frequencies are identical for all food items ranging from never to more than five times a day. Food specific portion sizes are presented by illustrations and/or by household measures such as glasses, cups, and spoons.

#### Qualitative module IDEE

A semistructured interview guide is used that includes topics related to grocery shopping and further ways of food provision, meal preparation, priorities and challenges related to nutrition in the family, financial aspects, assumptions about healthy nutrition, further roles of foods and meals (e.g. social and cultural aspects) and thoughts about how families can be supported in terms of their nutrition and related areas of life (Table 3).

**Table 3. table3-02601060241242159:** Themes of the IDEE interview guide.

**Main themes in IDEE**	**Complements** **(questions asked if not already elaborated by interviewee)**
(1) Everyday meals and meal preparation	Subjective priorities of interviewee and family members Ways of meal preparation Challenges in meal preparation Desired changes of diet Communal meals Eating out-of-home Child's desire to eat away from home
(2) Grocery shopping or other kinds of food provision and priorities	Challenges in food provision Criteria for decision making Strategies in case of temporarily lower budget Changes if budget would be larger
(3) Ideas about what is considered healthy nutrition	Healthy eating in the family Challenges for a healthy diet Situations when healthy eating is not priority Potential problems and solutions when wanting to increase intake of fruits and vegetables Problems and solutions when reducing sugar intake
(4) Further roles of eating in personal life	Potential functions of foods beyond nutrition Role of snacks
(5) Food and eating in social life	Occasions of eating with others, potential concerns If hosting guests: serving food, concerns or priorities Effects of financial situation on social life
(6) Measures to ease the burden for families	Means to facilitate everyday life Possible measures by the government Ranking of nutrition among current personal concerns
(7) Nutrition-related support measures	Situations where measures are needed Persons or institution who should offer support

#### Qualitative modules BEA

The World Café design (Brown et al., 2005) is used to identify experiences about healthy nutrition in everyday life from the perspective of parents and explore approaches to develop support measures. The moderator of the forum introduces participants to the World Café technique. Groups of three up to five participants sit around four tables, together with a table host. At first, all participants freely discuss about “good nutrition” (e.g. “What is good nutrition for you?”) for 7 minutes. Then, as described in Table 4, predefined questions relating to the following four themes are discussed: (1) barriers of a healthy diet, (2) facilitators of a healthy diet, (3) facilitators when adopting the perspective of a future moment, and (4) wishes concerning healthy nutrition and an elaboration of a given list of possible behavioral and environmental preventive measures. Each table host has a different set of open-ended questions relating to one of the four themes. After 20 minutes, participants change the table and mix up to a new discussion group.

**Table 4. table4-02601060241242159:** Discussion guide of the BEA World Café.

**Main themes in BEA**
What is good nutrition for you?
2) What makes it easier for you and your family to eat healthy in everyday life?
3) What makes it difficult sometimes for you and your family to eat well?
4) Let's assume we would have a look into the future: Today in 2 years you notice your family eats much healthier. What has changed? (Circumstances, behavior)
5) (A) If anything was possible: What would you wish for so that you and your family can eat better?
(B) Would you make use of the following support options? If yes: What would be important? If no: why rather not? Free of charge cooking class or workshop in your neighborhood Free of charge breakfast and lunch in schools and daycare centers Free of charge lunch for children during school holidays Free of charge or affordable warm meals, e.g. at a food bank More affordable fruits and vegetables for low-income families Nutritional counseling and presentations about nutrition

#### Quantitative module KENNER

An online survey (EFS Survey, Tivian XI GmbH) is performed on-site by using tablet computers. Participants needing assistance in using a tablet computer and participants with low literacy are interviewed.

Sociodemographics and health aspects are assessed by a slightly adapted version of questionnaires from the DEGS (Scheidt-Nave et al., 2012). Attitudes toward healthy nutrition (e.g. “Eating healthily is an important determinant of a long and healthy life” and “I am tired of listening what I should eat or should not eat”) are assessed by eight simplified items of Diehl's scale “Attitudes towards healthy nutrition” using a five-point Likert scale (strongly disagree to strongly agree) (Diehl, 2006). Questions regarding knowledge and usage of different types of measures were developed with various answer options such as recipe apps, nutrition-related websites, and school or childcare facility nutrition projects. In addition, specific programs or measures to promote a healthy diet are shown with the corresponding logo, for example, existing mobile applications, or governmental websites promoting activities around a healthy diet. Depending on the responses, participants are asked about reasons of nonusage or about evaluative aspects of the specific measures including, for instance, access and layout, comprehensibility, and suitability. Similarly, the awareness and practice of the dietary recommendations of the German Nutrition Society (DGE) are surveyed (“5 a day,” “10 guidelines for a wholesome diet,” “DGE nutrition circle,” and “The German Three-Dimensional Food Pyramid”).

Finally, participants are asked about topics they wish preventive measures to be related, their preferred type of nutrition-related preventive measures and the preferred way to be informed about such offers.

### Analyzes

#### Quantitative module BERNA

Descriptive analyzes provide information on the distribution of the nutritional and health aspects including nutrition-related expenses and the diet of individuals living in families at risk of poverty according to sociodemographic characteristics such as age, sex, origin/migration background, parental educational level, parental occupation and living in rural and urban areas. Mean, standard deviation, and median will be provided for continuous variables and absolute and relative frequencies with 95% confidence intervals based on bootstrapping will be given for categorical variables. Absolute amount of food consumption will be provided in gram per day or gram per week. In addition, the proportion of participants achieving cut-offs of the age- and sex-specific recommendations (for children and youths: “Optimised mixed diet” (Kersting et al., 2005), for adults: recommendations of the German Nutrition Society (Oberritter et al., 2013)) will be calculated. The Healthy Nutrition Score HuSKY will be calculated for adolescents (Kleiser et al., 2009). Relationships between the diet, food insecurity and diverse nutritional and health aspects will be analyzed by multivariate analyzes taking the clustering of the data into account (generalized linear mixed models and linear mixed models).

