## Methods

### Study design

MEGA_kids is a mixed-methods cross-sectional study combining four study modules (Table 1):
The first module (BERNA, “Nutritional survey among individuals living in households at risk of poverty with children”) contains a cross-sectional survey among children, youths, and adults living in households at risk of poverty. By this module, food intake, food insecurity as well as other nutritional and health aspects such as cooking skills, nutritional knowledge, and subjective health is assessed by standardized questionnaires. In addition, participants are asked to collect their cash receipts of food shopping over a period of 2 weeks.For the second module (IDEE, “Identification of factors influencing food security and nutritional quality from the perspective of adults living in households at risk of poverty with children”) a subsample of adults from BERNA is drawn with whom semistructured interviews are conducted about the food provision and preparation in everyday life as well as the social and health dimension of nutrition in their household.For the third module (BEA, “Needs of households at risk of poverty with children and approaches to develop behavioral and environmental support measures for a healthy diet“), another subsample of adults from BERNA is drawn and focus groups using the World Café technique are conducted to identify opinions and experiences, and generate ideas for tailored support measures for a healthy diet from the perspective of the adult target group.Finally, the fourth module (KENNER, “Knowledge and usage of nutrition-related preventive measures among adults of households with children at risk of poverty”) is a cross-sectional survey among parents living in households at risk of poverty about their knowledge regarding and usage of existing nutrition-related measures.

**Table 1. table1-02601060241242159:** Modules of MEGA_kids.

**Name**	**Sampling**	**Design**	**Duration**	**Sample size**
BERNA (“Nutritional survey among individuals living in households at risk of poverty with children”)	Multistage, partly randomized	Standardized survey (self-administered questionnaires + collecting cash receipts over 2 weeks)	ca. 20–40 min	1000 individuals (500 adults and 500 children) of 500 households

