### Study population

#### Quantitative module BERNA

The study population comprises children aged between 1 and 17 years as well as adults over the age of 18 years living in households at risk of poverty with children in rural and nonrural districts in Germany.

To illustrate the wider range of income-related risk of poverty, eligible households must meet at least one of the following criteria:
- household has an equivalized disposable income at or below the at risk of poverty thresholds (60% of the national median equivalized disposable income) and/or- household head receives social transfers including, for instance, unemployment pay II, and/or- household receives food assistance from a food bank.

Households of separated parents with shared custody are able to participate if at least one child lives for at least 15 of 28 days in this household. In households with more than one adult, the adult who is responsible for the majority of food shopping is allowed to participate.

The adult has to be sufficiently able to speak or write German, English, or Arabic. Adolescents must be able to speak or write German.

Information for children between 1 and 11 years are obtained by adults (parents), whereas adolescents between 12 and 17 years can participate themselves.

Households headed by a pregnant woman are excluded from participation. In addition, persons living in “collective living quarters” or other shared accommodations are excluded.

The sample of BERNA is expected to include 500 adults and 500 children aged between 1 and 17 years.

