#### Quantitative module BERNA

Participants of the BERNA survey are enrolled in three steps. In the first step, eleven districts throughout Germany are randomly drawn, stratified by the typology for rural areas of the Thünen Institute (Küpper, 2016). By combining the two dimensions rurality and socioeconomic condition, the Thünen Institute assigned each district to one of the following five types: nonrural, very rural and good socioeconomic condition, rural and good socioeconomic condition, very rural and worse socioeconomic condition and rural and worse socioeconomic condition (Küpper, 2016). For the purpose of this study, very rural and rural districts are combined resulting in three strata. Overall, five nonrural, three very rural/rural districts with good socioeconomic condition and three very rural/rural districts with worse socioeconomic condition are randomly drawn.

In the second step, facilities serving low-income population groups including, for instance, food banks (“Tafel”), job centers, family centers, social supermarkets, facilities providing employment measures for long-term unemployed individuals, and others are selected in each district. In addition, in each nonrural and very rural/rural district with worse socioeconomic condition, a random sample of five childcare facilities is drawn. Managers of all selected facilities receive written information about the study including its aim and procedure and are asked to allow the recruitment of families visiting the facility. A sampled rural district with good socioeconomic condition is included if at least one food bank and one other social facility are willing to participate and rural districts with worse socioeconomic condition and a nonrural area is included if at least one food bank, one childcare facility, and two social facilities agree to participate in the study. In doing so, a minimum of 38 facilities are included in the study.

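### BERNA proportions: the bootstrap is the only stated 95% interval method, and it can give zero-width or too-short intervals where a reported category has no, all or very few events

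*Protocol article*

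**What the plan says.** The BERNA paragraph under Analyzes names one interval method for categorical results: "absolute and relative frequencies with 95% confidence intervals based on bootstrapping will be given for categorical variables". The descriptive results are to be shown "according to sociodemographic characteristics such as age, sex, origin/migration background, parental educational level, parental occupation and living in rural and urban areas". The same paragraph adds that "the proportion of participants achieving cut-offs of the age- and sex-specific recommendations" will be calculated, without mentioning an interval or a breakdown for that outcome.

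Under Study population, "The sample of BERNA is expected to include 500 adults and 500 children aged between 1 and 17 years". Table 1 gives the same numbers: "1000 individuals (500 adults and 500 children) of 500 households".

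The article does not state the type of bootstrap, the unit resampled, the number or size of the subgroup categories, or any expected proportion.

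**The concern.** A nonparametric bootstrap can only rearrange what was observed. If a category has 0 of n, or n of n, every resample repeats that result and both limits equal the estimate. With a handful of events the resampled values stay close to the observed proportion, and the upper limit (for a rare category) tends to be too low. This is a small-count failure. Resampling facilities or districts instead of persons does not cure it, because clusters that contain no events also yield none.

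BERNA is mainly descriptive, so its proportions and their intervals are themselves the results, and the Discussion says that the study will guide officials and inform policy makers. An entry of 0% with limits 0% to 0% would claim a certainty that the data do not have. Empty or nearly empty categories are plausible in breakdowns by origin, occupation or age. They are also plausible at the extremes of multi-category items, such as the highest food-frequency option or severe social food insecurity, which requires all four items to be affirmed.

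**Working it through.** **The article's own figures.** 500 + 500 = 1000 individuals; 5 + 3 + 3 = 11 districts; 3 × 2 + (3 + 5) × 4 = 38 facilities. All agree with the text. No precision or coverage figure is stated, so there is none to reproduce.

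**Assumptions.** Independent respondents; percentile bootstrap with unlimited resamples; equal cells. The cell of 42 comes from an assumed grid of 6 age bands by 2 sexes: 500 / 12 ≈ 42. True proportions of 1% to 20% are also assumed.

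**Method.** For x events in n, the percentile limits are the 2.5% and 97.5% quantiles of Binomial(n, x/n), divided by n. Coverage at true p is the sum of Binomial(n, p) probabilities over those x whose limits contain p. Wilson and Clopper-Pearson were treated in the same way.

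**Worked case, n = 42.** The bootstrap limits, as counts, are 0 to 0 for x = 0; 0 to 3 for x = 1; 0 to 5 for x = 2; 0 to 7 for x = 3; and 1 to 8 for x = 4.
- True 2% (0.84 expected events): only x = 1, 2 and 3 cover. 0.367 + 0.154 + 0.042 ≈ 0.562. The main loss is x = 0, with probability 0.98^42 = 0.428.
- True 5% (2.1 expected): x = 1 to 6 cover. 0.256 + 0.277 + 0.194 + 0.100 + 0.040 + 0.013 = 0.880. The main loss is 0.95^42 = 0.116.

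**Coverage, percentile bootstrap / Wilson (%)**

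| n | p = 1% | 2% | 5% | 10% | 20% |
|---|---|---|---|---|---|
| 15 | 14.0 / 86.0 | 26.1 / 96.5 | 53.1 / 96.4 | 78.1 / 94.4 | 96.1 / 98.2 |
| 42 | 34.4 / 93.4 | 56.2 / 94.8 | 88.0 / 94.3 | 92.5 / 96.7 | 92.9 / 94.9 |
| 83 | 55.6 / 94.9 | 80.7 / 97.4 | 91.6 / 96.3 | 91.9 / 95.6 | 94.0 / 94.7 |
| 250 | 91.5 / 95.9 | 95.6 / 96.3 | 95.4 / 96.0 | 95.9 / 95.6 | 95.0 / 95.2 |
| 500 | 95.5 / 96.2 | 96.5 / 96.4 | 95.3 / 95.0 | 95.5 / 95.6 | 95.6 / 95.0 |

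The shortfall follows the expected count n × p and is large below about 2. Between 2 and 3 the tabulated values run from 88% to about 92%. Coverage is jagged because counts are discrete. On a finer grid from 10% to 50% at n = 42 it averages 93.5% but dips to 88.5% near 12%. The threshold of about 3 is therefore a guide and not a sharp limit.

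**Zero events.** The Clopper-Pearson upper limit for 0 of 42 is 1 − 0.025^(1/42) = 8.4%. Wilson gives 3.84 / (42 + 3.84) = 8.4%. The bootstrap gives 0%.

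**How often.** For one item in 12 cells of 42, the chance of at least one zero-width interval is 1 − (1 − 0.95^42)^12 = 77% at a true 5%, 13.5% at 10% and 0.1% at 20%. For one pooled group of 500 it is 0.99^500 = 0.7% at 1% and practically nil from 2%.

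**The case against.** The strongest objection concerns where the failure would appear. A reader might infer that attainment of the dietary recommendations will be tabulated by age and sex together, so that zero-width intervals are bound to be printed. The article does not say so. Age- and sex-specific describes the recommendations: each person can be judged against the cut-off for their own age and sex and the result pooled over up to 500 children or 500 adults. The breakdown variables are listed as examples and are never said to be crossed. No attainment or food-insecurity rate is given. This part of the objection stands in full: the cell of 42 and the low proportions are assumptions, and the difficulty largely disappears in larger cells or with commoner outcomes.

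Second, the type of bootstrap is not stated. The coverage percentages belong to the percentile version only. The collapse at 0 of n or n of n does not depend on that choice, as long as the resampling is nonparametric.

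Third, a condensed article may leave minimum cell sizes and the handling of zero counts to a fuller plan. A fuller plan may indeed contain such a rule. But the published sentence applies one method to all categorical variables without exception, and that stated rule fails in a foreseeable case.

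Fourth, absolute frequencies are to be printed as well, so a reader would see the zero count. That softens the consequence but does not make the interval correct.

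**Conclusion.** The concern holds in conditional form. Wherever a reported BERNA category has no events or all events, a nonparametric bootstrap interval has zero width. Where the expected count is below about 3, the percentile version under-covers: 56% at a true 2% and 88% at 5% for 42 independent respondents, against 95% and 94% for Wilson. Pooled results over about 500, and proportions of about 10% or more in cells of about 40 or more, are little affected, with coverage around 92% or better at the tabulated points.

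Whether such cells will be printed cannot be determined from the article, so the supportable wording is that these intervals may occur. The figures rest on assumed cell sizes, assumed proportions, the percentile method and independence. The issue is minor: it concerns the precision of descriptive reporting, and no hypothesis test or sample size depends on it.

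**What to change.** Add one sentence to the BERNA analysis: for proportions with few events or non-events (for example, fewer than about 10), report Wilson or Clopper-Pearson intervals computed at n divided by the design effect, and print no zero-width interval. The bootstrap can stay for other statistics and for well-filled categories.

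A cell with no events cannot supply its own design effect, so state where the value comes from, such as the whole-sample estimate for the same variable. The choice matters. For 0 of 42 and assumed design effects of 1, 1.5 and 2, the effective n is 42, 28 and 21, and the Clopper-Pearson upper limit 1 − 0.025^(1/n) is 8.4%, 12.3% and 16.1%.

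The cost is a sentence of wording and a standard routine, with no new data. The one downside is wider intervals in sparse cells.
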